***Omentectomy decreases insulin resistance:***

Epidemiologic *(Cefalu 1995, Shimokata 1989, Ferrannini 1997, Fujimoto 1999, Lamarche 1998, Carey 1996, O'Shaughnessy 1995)* studies (including our own) have correlated visceral fat with insulin insensitivity in both animals and humans. Several possible mechanisms have proposed this association. These include increased delivery of FFAs *(Bujalska 1997)* to the liver *(Bjorntorp 1990, Williamson 1996)* and/or abnormal expression of various cytokines (IL-6, TNF-α) and adipokines such as resistin, adiponectin, leptin and others *(Hotamisligil 1996, Steppan 2001).* Barzilai et al. *(1999)* demonstrated that surgical removal of visceral fat rapidly improved hepatic and peripheral insulin action in young rats and in rats predisposed to obesity and diabetes *(Gabriely 2002)*. Interestingly, removal of an equivalent amount of fat from the subcutaneous tissue in the same rats did not alter hepatic nor peripheral insulin sensitivities. Our recent studies in the conscious dog model (preliminary data) demonstrated that the removal of visceral fat resulted in improvement of insulin action in the absence of caloric restriction, challenging the notion that nutrient excess per se is the prominent cause of insulin resistance in obesity.

Thörne et al. *(2002)* randomized 50 non-diabetic morbidly obese subjects (BMI>35 kg/m2) to either adjustable gastric banding (AGB) alone or AGB plus partial removal of the greater omentum (omentectomy). The improvements in oral glucose tolerance, insulin sensitivity and fasting plasma glucose and insulin were 2-3 times greater in omentectomized subjects as compared to control subjects (P<0.05) and these were associated with a near 15% excess weight loss (p=0.07) over a two year period. There were no associated adverse effects related to omentectomy. It is important to note that the use of the adjustable gastric banding results in significantly less effective weight loss and less effective improvement in carbohydrate metabolism than RYGB and VSG. Ceelen and coworkers *(2003)* followed 625 subjects after laparoscopic AGB for three years and noted the median excess weight loss was limited to 47%. This is in comparison to a median excess weight loss up to 70% following RYGB.

1. **Rationale and Specific Aims**

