- Development of an intercurrent illness, condition, or procedural complication, which would interfere with the subject's continued participation.
- Subject is lost to follow-up

**If a subject fails to return for a scheduled visit, a documented effort must be made to determine the reason. This information should be recorded in the study records.**

Based on IRB recommendations, any adverse event that is identified and has not been addressed in the consent form must be added. The Principal Investigator will discontinue implementation of a protocol for the following reasons:

- There is clear evidence of harm or harmful side effects of the treatment or procedure;
- In the event that a serious adverse event occurs that increases the risk to participants, the study will be stopped and an investigation will be conducted and a findings report generated to the investigators, IRB, and the NIDDK;
- There is overwhelming evidence of the benefit of the treatment versus the control arm.

1. **Statistical Considerations**

**Describe the statistical power of the study, the confidence intervals and the method for analysis. Describe any possible deviations and their statistical impact.**

***Statistical Analysis:*** This protocol will provide information regarding basal carbohydrate, lipid and amino acid metabolism. Insulin sensitivity of hepatic glucose production will be determined using the 0.6 mU/kg.min insulin infusion rate. Peripheral glucose utilization will be determined using the 2.0 mU/kg.min insulin infusion rate *(Bonadonna 1990)*. The study will also provide information regarding insulin sensitivity of fatty acid metabolism (lipolysis and re-esterification). Studies in obese subjects and type 2 diabetic subjects demonstrated a right shift in the rates of insulin-stimulated suppression of lipolysis, hepatic glucose production and stimulation of peripheral glucose uptake. The insulin levels required were most sensitive for suppression of lipolysis followed by suppression in glucose production and then by insulin of stimulated glucose uptake *(Matthaei 2000)*.

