***Statistical Methods, Sample Size, and Power Estimates:*** We based sample size estimates on historical case volumes (>600 procedures per year), patient demographic distributions (70% Caucasian, 25% African American, 5% Hispanic, 80% female 20% male). Persons who consent to participate will be enrolled in both the short and long term phases of the study. We assumed attrition for the short-term phase, which entails data points through postoperative week four, to be negligible, and for the long-term study, which entails a two-year postoperative follow-up period, to be ~ 25% by postoperative month 24. We based this rate on reported attrition following bariatric surgery over a comparable time, and the rate is assumed to be comparable between experimental groups. Anticipated effect sizes were based on previous research or standard conventions for large, medium, and small effects *(Cohen 1988)*. Unless noted, power estimates were determined using standard methods and software (Power and Precision™ v. 2.0, nQuery Advisor™ v. 3.0) for non-directional tests at the 0.05 alpha level.

Demographic information such as age, race, and gender will be tabulated. Descriptive statistics, including means, standard deviations, and ranges for continuous measures, as well as percentages and frequencies for categorical measures will be presented. Statistical analyses will be performed using standard packages (SPSS or SAS).

**Specific Aim 1:** The short-term phase of the investigation will include a group of 66 Caucasians and group of 66 African Americans and Hispanics (each of the two groups randomized to 33 bariatric surgery and 33 bariatric surgery + omentectomy). The long-term phase of the investigation will include at least 100 patients (25 in each of the four racial and procedure groups).

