The long-term data, which entails five data points (preoperative, 1 month, 6 months, 12 months, and 24 months). Mixed effects modeling will be employed to determine whether patterns of individual change in outcome measures vary due to race, surgical procedure (bariatric surgery + omentectomy), and clinical covariates. Advantages of this method are that: (a) data from individuals with missing data may be included providing that the point(s) can be considered ‘missing at random’; (b) between-subject variation in the timing of assessment points can be accommodated (i.e. time is treated as a continuous variable); and (c) continuous or discrete time-sensitive covariates (e.g. weight loss, syndrome X symptom expression) can be incorporated. Follow-up analyses will be conducted on the sample having complete data through month 24 (expected n=100, 25 in each of four unique race by surgical procedure conditions) using methods described above for the short-term phase of the investigation. Simple and repeated contrasts will be employed to test within-subjects effects of time in relation to the preoperative measurement and the preceding time point, respectively. Assuming a within-subject correlation as low as 0.45, power is adequate (83%) to detect a small effect (d=0.3) of time on any contrast. Power to detect, for any contrast, medium (f=0.30) overall main effects of race and omentectomy and the race by omentectomy interaction effect is 84%. The power to detect large (d=0.81) effects of surgical procedure within each racial group (and of race within each surgical procedure group) for any contrast is 80%.

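### The long-term omentectomy contrasts are tested and powered in 24-month completers, the mixed model may adjust for weight loss, and the protocol does not say which analysis decides

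*Protocol*

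**What the plan says.** All of this is in the protocol's Statistical Considerations section unless noted.

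- **Sample.** In the short-term phase there are 66 Caucasian and 66 African American or Hispanic patients, "each of the two groups randomized to 33 bariatric surgery and 33 bariatric surgery + omentectomy". That is 132 patients, 33 in each race-by-procedure cell.
- **Attrition.** Loss is put "to be ~ 25% by postoperative month 24", and "the rate is assumed to be comparable between experimental groups". Reasons for dropout, and their relation to outcome, are not discussed.
- **Long-term model.** Mixed effects modelling comes first. It is to show whether change over five time points varies with race, surgical procedure and clinical covariates. Its listed advantages include keeping patients with missing data under missing at random, and that "continuous or discrete time-sensitive covariates (e.g. weight loss, syndrome X symptom expression) can be incorporated".
- **Completer analysis.** The text continues: "Follow-up analyses will be conducted on the sample having complete data through month 24". The expected size is 100, 25 per cell, and the method is the short-term repeated-measures analysis of variance. The contrasts against baseline and against the preceding visit follow, then the long-term power figures.
- **Aim 3.** The same two methods are reused for both phases, with a minimum long-term group size of 25. The time-varying covariates are not excluded.
- **Background, on omentectomy and insulin resistance.** In a cited randomised trial of gastric banding with or without partial omentectomy, the metabolic gains were larger with omentectomy, and "these were associated with a near 15% excess weight loss (p=0.07) over a two year period".

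**The concern.** Omentectomy is the randomised factor. Randomisation protects its comparison only while the patients analysed are those randomised and the model conditions on nothing that the operation could have changed. The long-term plan departs from this in two places.

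First, being a 24-month completer is a post-randomisation event. The protocol's safeguard is an equal dropout rate, but completers in the two arms can differ at equal rates if patients leave for different reasons. One possible route is in the protocol itself: the reasons for discontinuation include "Development of an intercurrent illness, condition, or procedural complication, which would interfere with" continued participation, and the Risks section says that removing the omentum may increase bleeding and will lengthen anaesthesia.

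Second, weight loss is measured after surgery, and on the protocol's own background it may be affected by omentectomy. A model containing it no longer gives the total effect of the operation. It gives a direct effect at best, and a distorted one if weight loss and the outcome share causes.

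At stake is whether the reported 6-, 12- and 24-month omentectomy effects can be read as randomised effects.

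**Working it through.** **Inputs from the protocol.** Tests are "for non-directional tests at the 0.05 alpha level". There are 33 patients per cell (132 in total), 25% attrition, 100 completers (25 per cell), f = 0.30 for main effects and interaction, and d = 0.81 for procedure within race.

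**1. Which patients the long-term power describes.** 132 × 0.75 = 99, so the stated 100 is the expected completer count.

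- Main effects and interaction: noncentral F with 1 and 96 df, λ = f²N = 0.09 × 100 = 9, gives 84.4% (stated 84%).
- Procedure within race: noncentral t with 48 df, δ = 0.81 × √(25/2) = 2.86, gives 80.1% (stated 80%).
- Time effect, d = 0.3 and r = 0.45: d/√(2(1 − r)) = 0.3/√1.10 = 0.286 with n = 100 gives 80.9% by t and 81.6% by normal approximation (stated 83%). This small gap does not bear on the point.

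The two omentectomy figures are therefore completer figures. No power is given for the mixed model.

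**2. Bias from selecting completers (assumed inputs).** In each arm the full mean is 0.75 × completer mean + 0.25 × dropout mean. The completer mean therefore exceeds the full mean by 0.25 × (completer mean − dropout mean). The bias in the arm comparison is 0.25 × the difference between arms in that gap.

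| Assumed difference in gap | Bias | Share of d = 0.81 |
|---|---|---|
| 0 | 0 | 0 |
| 0.5 SD | 0.25 × 0.5 = 0.125 SD | 15% |
| 1.0 SD | 0.25 × 1.0 = 0.25 SD | 31% |

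A normal selection model agrees. With the lowest 25% on a propensity to stay dropping out, the completer mean shifts by ρ × φ(z)/0.75 = 0.424ρ, where z is the 25th percentile of the standard normal and ρ is the correlation of outcome with staying.

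- ρ = 0.3 in one arm and 0 in the other: 0.127 SD. Two-sided type I error at 50 v 50 is about 10%.
- ρ = 0.3 and −0.3: 0.254 SD, and about 24%.
- Equal ρ and equal rates: 0.

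**3. Adjusting for weight loss (assumed inputs).** Let omentectomy shift weight loss W by 0.5. Let the outcome be 0.3 × omentectomy + 0.4 × W, with a shared cause of W and outcome of strength U and unit residual variances. The total effect is 0.3 + 0.4 × 0.5 = 0.50. Adjusted for W, the omentectomy coefficient is 0.3 − 0.5 × U²/(U² + 1).

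- U = 0: 0.30
- U = 0.5: 0.3 − 0.5 × 0.2 = 0.20
- U = 1: 0.3 − 0.5 × 0.5 = 0.05

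**4. Power after the change.** If all 132 contributed fully, power would be 92.8% for f = 0.30 (λ = 0.09 × 132 = 11.88) and 90.0% for d = 0.81 at 33 v 33. This is an upper bound. With 25% missing by month 24, the mixed model lies between it and the completer figures.

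**The case against.** The best defence is that the sounder analysis is already planned. The mixed model is named first and keeps incomplete cases, and the completer analysis is called follow-up. Sizing at the expected completer count is ordinary caution and does not make completers decisive. The covariates are optional, and Aim 1 asks which improvements merely follow weight loss, a question that needs weight loss in a model. The withdrawal list is generic and covers both arms. Bleeding is mainly a risk around the operation, and attrition to week four is taken as negligible. The cited banding trial reported no adverse effects from omentectomy, and its weight-loss finding had p = 0.07.

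Most of this stands and limits the point. It leaves three gaps: the two long-term analyses are not ranked, the contrasts at each visit are described only for completers, and Aim 3 reuses the methods without keeping weight loss out.

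Stronger readings are tempting, but the protocol does not support them:

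- A reader might infer that early data from patients who leave are thrown away. That is true only of the completer analysis. The mixed model keeps them, and week-four data are also analysed in all 132.
- A reader might infer that adjusting for weight loss would erode the stated 80% power. That figure belongs to the completer analysis of variance, which has no covariates. The covariates belong to the mixed model, which has no stated power.
- A reader might infer that the randomised comparison is already broken. Bias depends on how dropout and weight loss relate to outcome in each arm, which the protocol does not give.

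**Conclusion.** The point holds as a defect of specification that is worth correcting. The long-term omentectomy contrasts and their power sit in 24-month completers. The all-patient model is not made decisive, and post-randomisation covariates are allowed in the model that tests surgical procedure.

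The possible size is illustrative. Differentials of 0.5 to 1 SD between arms, which are assumptions without a source in the protocol, would give 0.13 to 0.25 SD of bias at 25% dropout. Equal rates with the same relation to outcome in both arms would give none. The weight-loss example shows the direction under assumed paths and is not an estimate for this trial. The mixed model is not a full cure, since it relies on missing at random, but it uses the early data of patients who leave.

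The point concerns the randomised omentectomy comparison. The race contrasts, and the Aim 3 comparison across racial groups, are not randomised under any analysis. A separate SAP, if one exists, may already rank the analyses; only the protocol was available.

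**What to change.** Amend the long-term analysis text as follows, and refer to it from Aim 3:

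- Take the long-term omentectomy contrasts, including those at 6, 12 and 24 months, from the planned mixed model fitted to all randomised, operated patients, with baseline covariates only. Time can stay continuous as planned, with the contrasts evaluated at those months.
- Make the complete-data analysis a sensitivity analysis.
- Label models that include weight loss or syndrome X expression as exploratory mediation for Aim 1, and do not report their omentectomy coefficient as the effect of omentectomy.
- Keep the stated omentectomy power (84% and 80%), described as conservative figures at the expected completer count.

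The cost is a wording change. It needs no more patients, visits or measurements.

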**Discuss the methods for ensuring participant privacy, and the methods for protecting privacy.**

Only research associates in our laboratories or those individuals directly involved with the study will have access to data. Information is for research purposes only and will be used for publication purposes. All participants will have their names concealed.

Access to identified patient information will be limited to the investigators listed within this IRB application. De-identified information with HIPAA identifiers removed will be available to other investigators following IRB approval. Confidentiality and security will be maintained for the database. The database is stored behind a firewall (in addition to the institutional firewall) with the highest level of protection, i.e. the same level of protection as the on-line hospital information system at Vanderbilt. This means that users must logon to a web server that sits between the institutional firewall and the firewall to the database, and only this application server is allowed to query the database. Only users approved through our institutional review board will be allowed access to patient identifiers. Other levels of authorization may exist for future approved users following IRB approval, e.g. access to de-identified data.

1. **Follow-up and Record Retention**

List the duration of the study. List the duration of record retention and the method for destruction or the possibility of indefinite archival of information.

The study is scheduled to last for 5 years. The samples and records will be stored for investigation for at least six years and may be indefinitely.

**Table of Events**

|  | **Before Surgery**  **(GCRC)** | **Surgery** | **4 wks**  **post-op** | **6 mon**  **post-op** | **12 mon**  **post-op** | **24 mon**  **post-op** | **3, 4, 5 yrs post op** |
| --- | --- | --- | --- | --- | --- | --- | --- |
| **History and Physical/Labs** |  |  |  |  |  |  |  |
| **DXA** |  |  |  |  |  |  |  |
| **Metabolic Chamber1** |  |  |  |  |  |  |  |
| **Chamber Blood Samples2** |  |  |  |  |  |  |  |
| **24 hour Urine** |  |  |  |  |  |  |  |
| **Metabolic Studies3** |  |  |  |  |  |  |  |
| **Omentum Biopsy4** |  |  |  |  |  |  |  |
| **Muscle Biopsy** |  |  |  |  |  |  |  |
| **Subcutaneous Fat Biopsy** |  |  |  |  |  |  |  |
| **SF 36 Questionnaire** |  |  |  |  |  |  |  |

1 Only subjects enrolled to be in the metabolic chamber

2 Only subjects enrolled to be in the metabolic chamber

3 May include insulin clamp (using tritiated glucose and/or deuterated glucose), amino

acid infusion for protein kinetics, and glycerol/palmitate infusion for lipolysis and FFA

kinetics

4 Only if other abdominal operations are needed
